### **7.2 Patient withdrawal criteria**

#### **Therapeutic failure**

Patients who meet therapeutic failure criteria will be withdrawn from the study. These criteria are defined as follows:

1. In patients receiving triple therapy randomly assigned at baseline, documented virological failure, i.e. the presence of a viral load greater than 500 copies/mL on 2 occasions 15 days apart, is considered as therapeutic failure.
2. Patients assigned to maintenance with LPV/r alone who reach the virological failure criterion will be considered as therapeutic failures if protease gene mutations exist, so that the patient cannot be reinduced with nucleosides and would discontinue the study because of the need of a therapy not based on LPV/r.
3. However, patients assigned to maintenance with LPV/r alone can be reinduced with the same nucleosides as withdrawn if no documented resistance to LPV/r exists. Thus, the following specific situation (a+b+c) will NOT be considered as therapeutic failure and will not lead to study discontinuation:
  - a) A patient in the maintenance arm with LPV/r alone has a viral load greater than 500 copies/mL on 2 occasions 15 days apart.
  - b) The genotypic resistance test shows no resistance to LPV/r.
  - c) The patient is reinduced with the same nucleosides as received before study entry and completes the follow-up period with an undetectable VL.

If this situation has occurred, and once patients are reinduced, they will be considered as therapeutic failures when the following conditions are met:

- 4 weeks after reinduction, viral load has not decreased by at least one decimal logarithmic unit
- and/or does not become undetectable again (<50 copies/mL) at 16 weeks of reinduction
- or if once on triple therapy they experience virological failure again.

In patients in whom a viral load ranging from 50-500 copies/mL is obtained, the above procedure will be followed.

After this viral load has been confirmed three times (2 weeks, 2 weeks, and 4 weeks), the following will be done:

- Patients in the monotherapy group and with no lopinavir resistance will be reinduced with the same nucleosides and the procedure in the previous paragraphs will be followed.
- Patients on triple therapy or in the monotherapy group but with lopinavir resistance: these will be considered as therapeutic failures, and after designing rescue treatment a follow-up visit will be scheduled 4 weeks after the end of study visit.

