#### **8.1.2 Secondary endpoints:**

- Assessment of treatment satisfaction of HIV+ patients who start monotherapy with LPV/r tablets versus triple therapy containing any PI using the CESTA questionnaire (Spanish Questionnaire of Satisfaction with Antiretroviral Treatment) [21] from the baseline visit to study week 24.
- Assessment of treatment adherence by HIV+ patients who start monotherapy with LPV/r tablets versus triple therapy containing any PI using the GEEMA questionnaire [22] and a visual analog scale (VAS) [23].
- Assessment of regimen tolerability and safety in HIV+ patients who start monotherapy with LPV/r tablets versus triple therapy containing any PI.
- Proportion of patients with a viral load <50 copies/mL of HIV RNA at 24 weeks in HIV+ patients who start monotherapy with LPV/r tablets versus triple therapy containing any PI. A viral load >500 copies/mL of viral RNA (HIV-1) confirmed at study week 24 will be considered as virological failure.
- Changes in immune response in HIV+ patients who start monotherapy with LPV/r tablets versus triple therapy containing any PI, as measured through the change in CD4+ cell count from the baseline visit to study week 24

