### **8.2.6 Criteria for treatment discontinuation or modification**

Study medication should be discontinued if the following occurs:

- Underlying disease that may significantly affect assessments of clinical status in the investigator's judgment.
- Unacceptable toxicity (toxicity that compromises the ability to continue with the protocol-specific procedures).
- At the request of the subject.
- Pregnancy
- Therapeutic failure, defined as 2 VL measurements > 500 copies/mL at least 2 weeks apart in the experimental group and/or genotyping with PI mutations that prevent continued treatment with LPV/r monotherapy.

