#### **B. Per protocol population (PP):**

This population will include all patients who complete the 24 weeks of follow-up.

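### Sections 7.2 and 8.2.6 define therapeutic failure on monotherapy incompatibly, and patients reinduced onto triple therapy are then counted as monotherapy results while controls with the same rebound are withdrawn

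*Protocol*

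**What the plan says.** Section 7.2 (Patient withdrawal criteria, Therapeutic failure) sets the consequence: "Patients who meet therapeutic failure criteria will be withdrawn from the study". It then treats the arms differently.

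- Control arm: "the presence of a viral load greater than 500 copies/mL on 2 occasions 15 days apart, is considered as therapeutic failure". No resistance result is needed and there is no reinduction route.
- Monotherapy arm with the same rebound: patients "will be considered as therapeutic failures if protease gene mutations exist".
- Monotherapy arm, no lopinavir resistance, previous nucleosides restarted, undetectable at the end of follow-up: "the following specific situation (a+b+c) will NOT be considered as therapeutic failure and will not lead to study discontinuation".
- Once reinduced, a patient fails if the viral load has not fallen by one log at 4 weeks, "and/or does not become undetectable again (<50 copies/mL) at 16 weeks of reinduction", or on a new virological failure.
- A viral load of 50 to 500, confirmed over 2, 2 and 4 weeks, follows the same split: reinduction for monotherapy without resistance, failure for everyone else.

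Section 8.2.6 lists, among the reasons to stop study medication: "Therapeutic failure, defined as 2 VL measurements > 500 copies/mL at least 2 weeks apart in the experimental group and/or genotyping with PI mutations".

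The virological endpoint in sections 8.1.2 and 12.3 is the proportion below 50 copies/mL at week 24, with this addition: "A viral load >500 copies/mL of viral RNA (HIV-1) confirmed at study week 24 will be considered as virological failure". The per-protocol set in section 12.1 reads: "This population will include all patients who complete the 24 weeks of follow-up". For patients who leave, section 12.4 uses the quality-of-life value obtained on leaving.

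**The concern.** Two sections give sites different instructions for the same patient under the same term. Section 8.2.6 joins its two conditions with and/or, so two values above 500 are enough without any resistance finding. That is exactly the patient whom item 3 of section 7.2 says is not a failure.

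The difference between arms then reaches the analysis. A monotherapy patient who needed nucleosides again can be below 50 copies/mL at week 24 because of triple therapy, and nothing in the protocol separates that result from suppression on monotherapy. The completers-only per-protocol set keeps this patient and loses the control who was withdrawn for the same rebound. The primary quality-of-life comparison is touched as well: one arm contributes a week-24 value on triple therapy, the other a value at exit.

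Finally, the 16-week reinduction criterion is long relative to 24 weeks of follow-up, so some patients may never reach the point at which their status is decided.

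**Working it through.** **1. The same event under the protocol's rules.** Event: two viral loads above 500, about two weeks apart, no lopinavir resistance.

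| Patient | Section 7.2 | Section 8.2.6 |
|---|---|---|
| Control | failure, withdrawn | no viral-load rule given |
| Monotherapy, reinduced, undetectable at end | not failure, stays in | failure, study medication stopped |

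The second row is a direct contradiction. With lopinavir resistance, section 7.2 counts failure in both arms, so the asymmetry concerns patients without resistance.

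**2. Where each patient ends up in the analysis.**

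| | Reinduced monotherapy patient | Withdrawn control |
|---|---|---|
| Below 50 at week 24 | can count as success, on triple therapy | no week-24 value; rule not stated |
| Per-protocol set | in (completes 24 weeks) | out |
| MOS-HIV and EQ-5D | week 24, on triple therapy | at exit |

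Example: a rebound above 500 first seen at week 12 is confirmed at week 14. If reinduction starts then, the MOS-HIV items at week 24 that ask about the past 4 weeks cover weeks 20 to 24, all on triple therapy. EQ-5D asks about the same day.

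**3. Timing of the reinduction criteria.** Inputs: scheduled viral loads at week 4 (monotherapy arm only), week 12 and week 24 (section 8.2); confirmation takes 2 weeks above 500 and 2 + 2 + 4 = 8 weeks at 50 to 500 (section 7.2); follow-up is 24 weeks. The wait for the genotype, g, is not given and is an assumption, varied from 0 to 4 weeks.

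Reinduction week = week first seen + confirmation time + g; then add 4 or 16. With g = 0, the most favourable case:

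| Level | First seen | Reinduced | 4-week check | 16-week check |
|---|---|---|---|---|
| >500 | 4 | 6 | 10 | 22 |
| >500 | 12 | 14 | 18 | 30 |
| >500 | 24 | 26 | 30 | 42 |
| 50–500 | 4 | 12 | 16 | 28 |
| 50–500 | 12 | 20 | 24 | 36 |
| 50–500 | 24 | 32 | 36 | 48 |

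- 16-week check: within 24 weeks in 1 of 6 cases. That case falls due at 22 + g, so it fits only if g is at most 2 weeks (3 with the one-week visit window).
- Put the other way, reinduction must start by week 24 − 16 = 8, so the rebound must be seen by week 8 − 2 = 6 (above 500) or week 8 − 8 = 0 (50 to 500).
- 4-week check: within 24 weeks in 4 of 6 cases at g = 0, and in 3 of 6 at g = 1 to 4 (4 of 6 at g = 1 with the window). It can be timed for most rebounds first seen at week 4 or 12.

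**4. A status the rules leave open.** A patient reinduced at week 14 and still detectable at week 24 does not meet the condition for not being a failure. Nor has this patient reached the 16-week limit, which is week 30. After week 24, section 8.2.4 offers only a conditional telephone call.

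**5. Size.** The protocol states no rebound or re-suppression rate, so no bias figure follows from it.

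**The case against.** The strongest defence is that section 7.2 governs withdrawal from the study, section 8.2.6 governs stopping medication, and the virological endpoint itself is worded identically in both arms. Comparing assigned strategies, planned reinduction included, is a legitimate choice: the primary objective in section 4.2.1 concerns patients who start simplification to monotherapy. Virology is secondary, section 12.4 plans description for secondary endpoints, and the handling of missing week-24 values can be left to the analysis plan. Annex 1 is a figure not available here and may give timings.

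Much of this stands, but it does not remove the contradiction. Both sections define therapeutic failure, and section 7.2 ties that term to withdrawal. A strategy comparison is a sound reading of the intention-to-treat analysis, but does not explain why a set called per protocol keeps patients back on triple therapy.

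Three stronger readings are tempting, and the documents do not support them.

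- A reader might infer a measurable artefact in favour of monotherapy. With assumed confirmed rebound r in both arms and re-suppression s, the section 7.2 labels differ by r × s: 0.10 × 0.80 = 8 points, and 2.5 (0.05 × 0.50) to 13.5 (0.15 × 0.90) over wider assumptions. But this uses the withdrawal labels, not the week-24 endpoint. Under the endpoint wording, a control withdrawn at week 14 is not a confirmed week-24 failure, and no missing-value rule is stated. The formula also ignores resistance and rebounds first seen at week 24, which cannot be confirmed before week 26. If rebounds were spread evenly over the three visits, the 8 points would become 0.10 × 2/3 × 0.80 = 5.3, before any resistance.
- A reader might infer that quality of life is biased towards monotherapy. No direction is shown: reinduced patients are back on nucleosides like the controls, which may dilute a benefit, and nothing shows that exit values are worse than week-24 values would have been.
- A reader might infer that the whole reinduction rule cannot be assessed. That holds for the 16-week limb only. A new virological failure can also be met after early reinduction.

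One imbalance runs the other way: only the monotherapy arm has a week-4 viral load, three scheduled looks against two. Any replacement endpoint has to allow for it.

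**Conclusion.** Sections 7.2 and 8.2.6 contradict each other on two viral loads above 500 without resistance in the monotherapy arm. This must be reconciled; which rule is clinically right is not judged here.

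The analysis consequences should be fixed too. Patients back on triple therapy can count as monotherapy successes at week 24, enter the per-protocol set and supply week-24 quality of life, while controls with the same rebound leave. How much this matters depends on how many monotherapy patients rebound without resistance and are re-suppressed, which the protocol does not say. Neither a size nor a direction for quality of life is claimed.

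The timing result is firm for the 16-week criterion: it falls due within follow-up in one of six scheduled cases, and only if the genotype wait is at most 2 weeks (3 with the visit window). It rests on detection at scheduled visits and on the confirmation intervals in section 7.2.

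**What to change.** 1. Reconcile section 7.2 with section 8.2.6. Reconcile the 16-week criterion with the 24-week follow-up as well, or state how patients who have not reached it are classified at week 24.
2. Analyse virology with one definition in both arms that does not depend on management. Success is below 50 copies/mL at week 24 with no antiretroviral added or changed for virological reasons; withdrawal for rebound or a missing value is not success. Report suppression after reinduction as a separate outcome. Because week 4 is measured in one arm only, add a sensitivity analysis based on the visits both arms share, weeks 12 and 24.
3. Exclude reinduced patients from the per-protocol set, or end their per-protocol contribution at reinduction.
4. Where feasible, amend the follow-up rule so that MOS-HIV and EQ-5D are also collected at week 24 from patients withdrawn for failure.

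Cost: amended wording in sections 7.2, 8.1.2, 8.2.6, 12.1 and 12.3. Item 4 is more than one extra questionnaire, because withdrawn patients have no routine week-24 visit; it changes the follow-up rule for those patients. The monotherapy success rate may look less favourable under item 2.

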### **Intolerance**

A serious adverse effect as defined in section 7.7 (Scheme modification criteria for toxicity).

## **7.2 PRIOR AND CONCOMITANT TREATMENT**

Patients will continue to receive their concomitant medications as prescribed. Any concomitant medication should be recorded in the Case Report Form (CRF). In addition, any diagnostic, therapeutic, or surgical procedure performed during the study period should be recorded, including the date, indication, description of procedure(s) and any clinical finding.

In order to guarantee patient safety, the following medications not recommended concomitantly with Kaletra will be excluded:

Kaletra®. Contains lopinavir/ritonavir, two inhibitors of the P450 CYP3A isoform, and should therefore not be administered together with drugs whose clearance largely depends on

CYP3A and for which an increase in plasma levels is associated with serious and/or life-threatening effects. Such drugs include astemizole, terfenadine, oral midazolam, triazolam, cisapride, pimozide, amiodarone, ergot alkaloids (e.g. ergotamine, dihydroergotamine, ergonovine, and methylergonovine), and vardenafil.

Herbal drugs containing St. John's wort (*Hypericum perforatum*) should not be used while lopinavir and ritonavir are being taken because of the risk of reducing plasma levels and clinical effects of lopinavir and ritonavir. Rifampin should not be used in combination with Kaletra® because it may markedly decrease lopinavir concentrations and thus significantly decrease its therapeutic effect.

If the patients need to start treatment with any of the excluded medications, the study coordinator should be consulted before it is started.

### **7.3 DESCRIPTION OF STUDY DRUGS**

#### **Description and handling of Kaletra®:**

##### **Formulation:**

Each film-coated tablet of Kaletra® contains 200 mg of lopinavir and 50 mg of ritonavir as booster. Kaletra® 200/50 mg tablets are yellow coated tablets having engraved the Abbott logo and "KA". Excipients: each tablet contains copovidone, sorbitan laurate, colloidal anhydrous silica, and sodium stearyl fumarate. See the product label for additional information.

##### **Packaging and labeling:**

PVC/fluoropolymer blisters. Each carton contains 5 aluminium blisters with 8 film-coated tablets each (40 tablets). Each package contains 3 cartons (120 tablets).

##### **Storage and handling:**

This product requires no special storage conditions.

### **7.4 SUPPLY OF STUDY DRUG**

During the study conduct, Kaletra will be provided (at no cost for the hospital) to any patient who needs to start treatment with this medicinal product because of participation in the study. The medication will be identified as "trial medication", and commercial labeling will therefore not be used.

Annex 2 provides a schematic application process for medication, and the re-labeling of medication for clinical use only.

## **8. STUDY CONDUCT AND EFFICACY ASSESSMENT**

### **8.1. STUDY ENDPOINTS AND MEASUREMENT INSTRUMENTS**

#### **8.1.1 Primary endpoint:**

- Changes in quality of life at 24 weeks (from the baseline visit) based on the parameters of the Medical Outcomes Study HIV Health Survey (MOS-HIV) and the EuroQol 5D visual analog scale (EQ-5D)[20].

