## 1. **SYNOPSIS**

1. Sponsor identification: SAEI  
Sociedad Andaluza de Enfermedades Infecciosas  
(Andalusian Society of Infectious Diseases)
2. Title of clinical trial: A randomized, open label clinical trial to compare the quality of life of HIV+ patients who start monotherapy with LPV/r tablets versus triple therapy containing a boosted PI.
3. Protocol code: SAI-CDV-2009-01
4. EudraCT code: 2009-014430-25
5. Name and qualification of monitors: Effice spi S.L.  
[name]  
[name]
6. Phase of clinical trial: Phase IV
7. Objectives  
Primary objective: To compare the quality of life of patients who start monotherapy with lopinavir/ritonavir® (LPV/r) tablets versus patients on triple therapy containing any boosted protease inhibitor (PI).  
Secondary objectives:
  1. Assessment of virological efficacy of monotherapy based on LPV/r tablets versus triple therapy containing any PI.
  2. Assessment of changes in immune response in HIV+ patients who start monotherapy with LPV/r tablets versus triple therapy containing any PI.
  3. Assessment of treatment satisfaction of HIV+ patients who start monotherapy with LPV/r tablets versus triple therapy containing any PI.
  4. Assessment of treatment adherence of HIV+ patients who start monotherapy with LPV/r tablets versus triple therapy

containing any PI.

5. Assessment of regimen tolerability and safety in HIV+ patients who start monotherapy with LPV/r tablets versus triple therapy containing any PI.

8. Design: A Phase IV national, multicenter, controlled, randomized, open label, parallel-group, comparative clinical trial

9. Randomization process: Randomization will be centrally performed.

10. Treatment groups: Treatment:  
Patients will be randomized in a 1:2 ratio to two groups, A and B respectively.

**Control group (A):** Patients will continue on triple antiretroviral therapy based on any PI boosted with ritonavir.

**Experimental group (B):** Triple antiretroviral therapy based on any PI boosted with ritonavir will be switched to LPV/r monotherapy.

Central randomization will be performed.

11. Disease under study: HIV infection

12. Primary endpoint: Quality of life, as measured by the MOS-HIV and EQ-5D questionnaires, of patients who start monotherapy with lopinavir/ritonavir (LPV/r) tablets versus patients on triple therapy containing any boosted protease inhibitor (PI).

13. Number of subjects: 390 (260 in experimental group B and 130 in control group A)

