### ***Sample size and rationale***

In a similar study population (e.g. HIV+ patients with an undetectable viral load, i.e. < 50 copies/mL of HIV-1 RNA), the mean baseline quality of life score measured with the MOS-HIV questionnaire was 61.84 [24]. As standard deviation is not available, we assume for all calculations that standard deviation will be the highest score minus the lowest score in the quality of life dimension (e.g. 100) divided by 5, which gives 20. This standard deviation of 20 is the same as found in HIV-infected asymptomatic patients, patients with AIDS-related symptoms, or patients with AIDS and a CD4 cell count <100 [25]. Assuming, then, that quality of life will remain unchanged in patients assigned to the control group (maintaining current antiretroviral therapy) and will improve by 10% (e.g. to scores of 68.02) in patients assigned to the experimental group (LPV/r® as monotherapy), with a 1:2 ratio, an 80% statistical power, and a two-sided alpha of 0.05, 372 patients would be required, 248 randomized to the experimental group and 124 randomized to continue on the current antiretroviral therapy.

Assuming 7% follow-up losses, the final sample size required will be of 260 patients for the experimental group and 130 patients for the control group, i.e. a total of 390 patients.

Because the triple antiretroviral therapy based on a PI boosted with ritonavir (control treatment) has been widely studied for a practical sense, it has been considered to allocate the sample to twice the experimental treatment (1:2, respectively) [24 ], [26].

This distribution of the sample (1:2) compared with the distribution of equal groups (1:1) ensures greater security in the contrast of the study to a possible greater variability of response in the quality of life in the experimental group since this group is expected to more patients with diarrhea to begin new therapy. [27]

Also it will provide an improved accuracy in estimating mean and smaller confidence intervals, for example, more than 1% in the estimated proportions near 50%.

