### **12.2. Primary endpoint**

- To compare the quality of life from baseline to 24 weeks in patients who start monotherapy with LPV/r tablets versus patients on triple therapy containing any boosted protease inhibitor (PI) using the Medical Outcomes Study HIV Health Survey (MOS-HIV) and the visual analog scale EuroQol 5D (EQ-5D).

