#### **12.4. Statistical methods.**

The statistical tests to be used and the specific study of each variable included will be described in detail in the Statistical Analysis Plan that will be prepared before the database is locked. However, a brief description is given below.

All analyses will be performed using statistical software SPSS, version 15.0 or higher. All statistical tests will be two-sided, with a significance level of 0.05.

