#### **Statistical analysis**

Baseline characteristics of study groups will be compared using an analysis of variance (ANOVA). The mean, median, standard deviation, and range will be provided for continuous variables, and the distribution of absolute frequencies and percentages will be given for discrete variables. When required, 95% confidence intervals will be calculated. Discrete variables will be compared using a Chi-square test.

For quality of life analysis, the primary population will include all patients with data available from baseline up to at least one post-baseline visit (e.g. the intention-to-treat population).

In case of patient abandonment is taken as a post-treatment evaluation the one obtained at the time of abandonment. If there is no post-treatment evaluation as a neutral value, baseline observation value will be carried forward until month 24 or the time of abandonment (Baseline Observation Carried Forward).

The main deadline to study results will be week 24 of the study. An analysis of covariance (ANCOVA) will be used for quality of life comparison. The model will include the baseline values for the items in the MOS-HIV questionnaire, age and sex as covariates, in the control and study groups. For primary endpoint analysis, the values in the MOS-HIV and EQ-5D questionnaires in the different weeks as compared to baseline will be provided for each treatment group.

An analysis of covariance (ANCOVA) will be used for comparisons between both treatment groups.

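### The primary endpoint rests on at least two unranked measures with no success rule, while the sample size covers one comparison on one MOS-HIV score that is not clearly identified

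*Protocol*

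**What the plan says.** The primary endpoint is given in three places in the protocol, each time on two instruments:

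- Synopsis, item 12: "Quality of life, as measured by the MOS-HIV and EQ-5D questionnaires".
- Section 8.1.1: change at 24 weeks "based on the parameters of the Medical Outcomes Study HIV Health Survey (MOS-HIV) and the EuroQol 5D visual analog scale".
- Section 12.2: comparison from baseline to 24 weeks "using the Medical Outcomes Study HIV Health Survey (MOS-HIV) and the visual analog scale EuroQol 5D (EQ-5D").

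The synopsis names the EQ-5D questionnaire, which in Annex 3 has five descriptive dimensions and a visual analog scale. Sections 8.1.1 and 12.2 name only the scale. The MOS-HIV parameters are plural, and they are neither listed nor counted.

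On testing, section 12.4 states: "All statistical tests will be two-sided, with a significance level of 0.05". It plans an ANCOVA between groups and says that for the primary endpoint "the values in the MOS-HIV and EQ-5D questionnaires in the different weeks as compared to baseline will be provided for each treatment group". It gives no hierarchy, no split of alpha, and no rule on whether one or all measures must be significant.

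The sample-size section starts from a single figure, "the mean baseline quality of life score measured with the MOS-HIV questionnaire was 61.84", and takes its standard deviation from "the highest score minus the lowest score in the quality of life dimension", divided by 5. It concludes that "with a 1:2 ratio, an 80% statistical power, and a two-sided alpha of 0.05, 372 patients would be required". It contains no EQ-5D input and no allowance for a second comparison.

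**The concern.** Error rate and power belong to a decision rule, and here the rule is missing. The endpoint names at least two measures, the significance level is the same for every test, and the size was worked out for one test. Whoever reports the trial would have to supply the rule afterwards.

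The timing makes this matter more. The trial is open label and the outcome is reported by the patient. The SAP, to which section 12.4 leaves the details, is due only before database lock. If the deciding measure is settled that late, it can be settled after outcome data have accrued by known treatment arm. At stake is what counts as a positive trial.

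**Working it through.** **Inputs from the sample-size section.** Control mean 61.84; experimental mean 68.02; difference 68.02 − 61.84 = 6.18; SD 100/5 = 20; two-sided alpha 0.05; power 80%; allocation 1:2.

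**Step 1: reproduce the plan's figure for one comparison.**
n(control) = (1 + 1/2) × (1.960 + 0.842)² × 20² / 6.18² = 1.5 × 7.849 × 400 / 38.19 = 123.3, rounded up to 124. The experimental group is 2 × 124 = 248, and the total is 372. This matches the protocol exactly.
Standard error = 20 × √(1/124 + 1/248) = 2.20. Standardized difference = 6.18/2.20 = 2.81. Power = Φ(2.81 − 1.96) = 80.2%.
The arithmetic is right for one test.

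**Step 2: count the measures.** Two is the least that the text allows: one MOS-HIV score and the EQ-5D scale. The correlation between them is not given, so I assume a range from 0 to 0.8. The correlated cases below were simulated with 300,000 pairs of normal test statistics.

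**Step 3: either measure may win, each at 0.05.**
Independent: 1 − 0.95² = 9.75%.
Simulated: 9.0% at correlation 0.5 and 7.9% at 0.8.
The error rate fails. Power to win on at least one measure is not below 80%.

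**Step 4: both must win, each at 0.05.** I assume the same standardized effect on each measure, because the protocol gives no EQ-5D effect.
Independent: 0.802² = 64%.
Simulated: 69% at correlation 0.5 and 73% at 0.8.
The error rate stays at or below 5%, and power fails. With independent measures, 80% power would need 486 evaluable patients (162 + 324).

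**Step 5: either may win, Bonferroni at 0.025 each.**
Power per comparison = Φ(2.81 − 2.24) = 71.5%. Restoring 80% for each comparison needs 450 evaluable patients.

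| Rule for two measures | False-positive rate | Power at 372 |
|---|---|---|
| Either, at 0.05 each | 7.9-9.75% | at least 80% for one or more wins |
| Both, at 0.05 each | at most 5% | 64-73% |
| Either, at 0.025 each | at most 5% | 71.5% per comparison |
| One named score only | 5% | 80.2% |

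Only the last row delivers both stated properties at 372, and the endpoint definition does not describe it.

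**The case against.** The strongest reply is that section 12.4 calls itself a brief description and leaves the tests for each variable to a SAP that is not shown. Scoring of the MOS-HIV, the choice of summary score and the handling of multiplicity are often placed there. Section 12.4 also speaks of one model, adjusted for MOS-HIV baseline values, age and sex, and says of the primary endpoint that values will be provided, which is the language of reporting. One could conclude that a single MOS-HIV score was intended all along.

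Part of this stands: the absence of a scoring algorithm or a multiplicity procedure is no fault in the protocol. But the endpoint definition, the common 0.05 and the sample size are all fixed in the protocol, and they do not fit one another. A SAP that set a hierarchy would still leave the synopsis and sections 8.1.1 and 12.2 to be brought into line.

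Three stronger readings are tempting, and the documents do not support them:

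- A reader might infer that the trial may be declared positive on whichever measure is significant. No such rule is written; the rule is unstated.
- A reader might infer that the 5% and the 80% both fail. No single rule considered above breaks both: unadjusted either-wins costs error control, and both-must-win costs power.
- A reader might take one test per MOS-HIV domain and arrive at a false-positive rate of several tens of percent. The protocol states neither how many domains there are nor how many would be tested, and the 35 items in Annex 3 are not a count of tests. More than two tests would be worse than the figures above, but by how much cannot be read from the protocol.

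**Conclusion.** The concern holds in this form. The primary endpoint has at least two unranked measures and no any-or-all rule, and the sample size serves one comparison. With two measures, the false-positive rate is about 8-10% if either may win, or power at 372 is about 64-73% if both must. Which property is lost depends on a rule that the protocol does not give.

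These figures assume exactly two tests and a correlation between 0 and 0.8. The power figures also assume equal standardized effects. The 372 itself is not in error.

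A second gap is that the score used for sizing cannot be matched with certainty to a named endpoint. The text moves from a quality of life score on the MOS-HIV to a quality of life dimension. That could be an overall score or one dimension, and item 12 of the questionnaire is a single five-category question on quality of life. I cannot tell from the protocol which is meant.

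**What to change.** In the synopsis, section 8.1.1 and section 12.2:

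1. Identify by name the MOS-HIV score to which the 61.84 refers, and make its change from baseline to week 24 the sole primary endpoint, tested at two-sided 0.05. The sponsor must supply the name. The 372 evaluable patients and 80% power then stand under the plan's own assumptions.
2. Make the EQ-5D visual analog scale the first secondary endpoint, tested only if the primary succeeds, and describe the EQ-5D in the same way in all three places.
3. Report the other MOS-HIV scores with confidence intervals and without confirmatory claims.

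The cost is protocol wording, with no additional patients on this account. The downside is that no other score can support a confirmatory claim if the named one is not significant.

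Keeping two primary measures is also possible, but the rule must then be written down and the trial re-sized: about 450 evaluable patients with a Bonferroni split, or about 486 if both must win and the measures are independent.
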